### Sample size

No power analysis was done for this field experiment. First, our implementing partner (the ASF) gave us a strict limit on the number of audits they would allow us to randomize. Second, a power calculation would have been complicated by the number of primary outcomes in this exploratory trial. Third, not enough data from relevant prior studies were available to inform the statistical sample size calculation. Given these restriction we powered the study by using an unbalanced block design, which improves covariate balance and efficiency. The only limit on the number of controls was our own budget, and concerns for bias if the study became too unbalanced. Hence the sample size was determined *a priori* to 85 municipalities. Finally, blocks with four or more units may have some advantages relative to pair matching [45, 46]. As an additional check we will do *ex post* power calculations for minimum detectable effect sizes for key outcomes.

### Blinding

Whereas researchers and ASF management in Mexico city are fully aware of treatment allocations, the survey firm and research assistants collecting outcome data were kept blinded to the allocation. The researchers took no specific measures to ensure field auditors carrying out the audits were blinded to the allocation. Similarly, municipal staff are clearly aware whether they are being audited or not, but there is not reason to expect them to know they are part of an experiment. Finally, because the researchers are not blind to the allocation they will carry out the data analysis according to the detailed analytical plan in Additional file 2.

### Statistical methods

Because our sample is relatively small and we are concerned about power our approach is to start by asking very little of the data, and then ask progressively more depending on the answers to previous queries. The inferential framework is as follows: *Sharp null hypothesis test*: We begin by testing the sharp null of no effect on any unit against the alternative of some effect (e.g. change in location, scale, or distribution). These tests can tell us whether the treatment has an effect, but they are silent as to the magnitude and variability of the effect.*Visual inspection of outcome distributions*: We plot histograms, box plots, and density plots, as befits the type of measurement, for the outcomes of interest across treatment arms.*Descriptive inference*: We describe measures of central tendency, like experimental group averages and their standard deviation, along with the difference across averages and their standard deviations (so-called ATEs). For the latter we ignore the covariance term in Var (*Y*_*C*_−*Y*_*T*_)= Var (*Y*_*C*_) + Var (*Y*_*T*_)− 2 Cov (*Y*_*C*_,*Y*_*T*_) as it is not observed, where *Y* is the outcome of interest and subscripts refer to treatment and control conditions. This provides a more conservative estimate.*Modeling*: To generate estimates of causal effects and confidence intervals we need to assume non-interference and a model of causal effects. We check the nature of the underlying model assumptions by performing model diagnostics including testing normality of residuals, homoscedasticity, plotting residuals against predicted outcomes, and comparing the actual experimental data to fake data generated from the estimated model [47, 48].

Because the treatment was randomized with known probabilities we rely on randomization tests of the sharp null of no effect on any unit [49]. The specific randomization statistic chosen will be appropriate to the category and distribution of the outcome measures. We will use sequential partitioned hypothesis testing to address the multiplicity of analyses and outcomes and control the Type I error rate [50, 51]. We will let exploratory data analysis and model checking determine whether we model the outcome by inverting randomization tests or via robust OLS estimation, though our default is to rely on additive effects and inversion of sharp null hypothesis tests (see Annex A). Finally, whereas the treatment was randomized to municipalities, some outcome variables are measured at the level of individual municipal administrators. At this level the treatment can be thought of as cluster randomized. We will analyze these data at the individual level and check for robustness by comparing inferences to a differences in total outcomes estimator and to aggregating individual level at the municipal level [52]. A detailed analytical plan is available as Additional file 2.

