**Methods/Design:**

The AUDIT study is a block randomized, controlled, three-arm parallel group exploratory trial. A convenience sample of 5 municipalities in each of 17 states in Mexico (*n*=85) were block randomized to be audited by federal auditors (*n*=17), by state auditors (*n*=17), and a control condition outside the annual program of audits (*n*=51) in a 1:1:3 ratio. Replicable and verifiable randomization was performed using publicly available lottery numbers. Audited municipalities were included in the national program of audits and received standard audits on their use of federal public service infrastructure grants. Municipalities receiving moderate levels of grant transfers were recruited, as these were outside the auditing sampling frame – and hence audit program – or had negligible probabilities of ever being audited. The primary outcome measures capture compliance with the grant program and markers for the causal mechanisms, including deterrence and information effects. Secondary outcome measure include differences in audit reports across federal and state auditors, and measures like career concerns, political promotions, and political clientelism capturing synergistic effects with municipal accountability systems. The survey firm and research assistants assessing outcomes were blind to treatment status.

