## Methods/Design

### Trial design

The AUDIT study is a block randomized, three-arm parallel group, exploratory trial on a convenience sample of 85 municipalities in Mexico. Blocking was done by state across 17 states, with five municipalities per block. Using non-uniform random assignment and a 1:1:3 blocking ratio we assigned one municipality per block to be audited by the ASF, another by the EFSL, and the remaining three municipalities to the control condition (no intervention). Our reporting of the trial design follows the CONSORT 2010 Checklist [39, 40] (See Additional file 1). The trial received an ethics approval by Yale University’s Human Subjects Committee (ref: 1106008610), and is registered with the International Standard Randomised Controlled Trial Number Register (ISRCTN22381841) and the Experiments in Governance and Politics Network (No:20121031). All end line survey participants are required to give informed consent.

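### The standard deviation given for each ATE is that of a difference between two single outcomes, not of the difference in averages; the effect is confined to the descriptive step

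*Protocol article*

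**What the plan says.** The Statistical methods section of the protocol article sets out four steps: sharp-null tests, visual inspection, descriptive inference and modelling. The third step will give group averages with their standard deviations, "along with the difference across averages and their standard deviations (so-called ATEs").

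The variance for this comes next: "For the latter we ignore the covariance term in Var". The identity printed at that point is Var(Y_C − Y_T) = Var(Y_C) + Var(Y_T) − 2Cov(Y_C, Y_T), and the ground given for dropping its last term is that the covariance cannot be seen in the data. The symbol is defined in the same sentence: Y "is the outcome of interest and subscripts refer to treatment and control conditions". The step closes with "This provides a more conservative estimate".

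The arm sizes are in the abstract. Municipalities "were block randomized to be audited by federal auditors (*n*=17), by state auditors (*n*=17), and a control condition". The control group is put there at 51 municipalities, which makes the allocation 1:1:3. The Trial design section adds: "Blocking was done by state across 17 states, with five municipalities per block".

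Confidence intervals belong to the fourth step. By default they come from inverting sharp-null tests under additive effects, with robust OLS as the alternative.

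**The concern.** The quantity reported is a difference between averages, but the variance printed for it is that of a difference between two single outcomes. No arm size appears in it. A standard deviation of this kind stays the same however many municipalities are studied, whereas the uncertainty of an ATE falls as the arms grow.

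The descriptive step gives the first numerical size and spread of each effect, after tests that the article itself describes as silent on magnitude and variability. A reader who sees a standard deviation beside an ATE, described as conservative, will probably take it for a cautious standard error. On that reading it could seem to contradict a randomization test that rejects the null for the same outcome, although the two figures measure different things.

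**Working it through.** The article states no numerical SD, standard error or power figure, so there is nothing to reproduce. The allocation is consistent: 17 × 5 = 85 = 17 + 17 + 51.

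**Inputs**
- Arm sizes of 17 (federal audit), 17 (state audit) and 51 (control), from the abstract.
- Contrasts: federal v state audit (17 v 17), one audit arm v control (17 v 51), and both audit arms pooled v control (17 + 17 = 34 v 51). Pooling is an assumption, suggested by the reference to treated municipalities in Table 1.
- Outcome SD σ, equal in both arms. This is an assumption, since the article gives no SD; a common σ cancels in the ratio.

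**Formulas**
- As printed, covariance dropped: √(σ² + σ²) = 1.414σ for every contrast.
- Standard error of a difference in averages, blocking ignored: σ√(1/n_T + 1/n_C).

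| Contrast | As printed | Standard error | Ratio |
|---|---|---|---|
| 17 v 17 | 1.414σ | √(1/17 + 1/17) = 0.343σ | 4.12 |
| 17 v 51 | 1.414σ | √(1/17 + 1/51) = 0.280σ | 5.05 |
| 34 v 51 | 1.414σ | √(1/34 + 1/51) = 0.221σ | 6.39 |

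**Sensitivity**
- Treated-to-control variance ratio from 0.25 to 4: the multiple stays at 4.12 for 17 v 17, and runs from 6.04 down to 4.43 for 17 v 51 and from 6.81 down to 6.04 for 34 v 51.
- Simulated 1:1:3 assignment in 17 blocks of five, no effect, uniform probabilities within block, 20,000 re-assignments of one generated data set: 3.96, 4.87 and 6.16 (in the order of the table) when outcomes were generated with no variance between states, and 4.69, 5.74 and 7.24 with 30% of it between states.
- Individual-level survey outcomes, 17 v 51, assuming 2 to 5 respondents per municipality and an intracluster correlation of 0.1 to 1: 5.05 to 9.54.
- The non-uniform lottery probabilities were not modelled. By the article's own count they affect 4 federal and 3 state assignments.

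**Does reading Y as an arm average repair the sentence?** Let S_C² and S_T² be the variances of the two potential outcomes over a fixed set of N units, and S_CT their covariance. Under complete randomization, the covariance of the two arm means is −S_CT/N. If a unit's two potential outcomes are positively related, this is negative, so the term −2Cov is positive and dropping it makes the variance smaller, not larger. The familiar conservative result comes from using S_C²/n_C + S_T²/n_T, which is a different step and is not stated. At unit level the claim does work: with positively related potential outcomes, dropping −2Cov raises the variance of the unit-level difference.

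**The case against.** The best defence is that the identity was meant only to explain why a covariance is left out. The sentence refers back to the difference in averages, and the usual argument for that difference also involves a covariance of potential outcomes that cannot be observed. On this view Y stands loosely for an arm average, and the divisors, block adjustment and weights are in Additional file 2, which is not shown. This is possible, and the reason given for dropping the covariance does not by itself settle the matter. But the reading conflicts with the printed definition of Y and, as shown above, does not yield the stated reason for conservatism. Nor is this a detail left to another document: the article prints a formula, and it does not match the quantity it is attached to.

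A second defence is that the authors wanted to describe how variable the effect is across units. That is also possible. The figure would then be mislabelled, and it would describe that variability only under zero covariance. With equal SDs and a constant additive effect, which is the article's own default model, the true unit-level spread is √(1 + 1 − 2)σ = 0, while the formula gives 1.414σ.

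A reader might infer that the trial's statements of uncertainty will be four to six times too wide and that every effect will look uninformative. The article does not support that. The sharp-null tests, the inverted-test or robust OLS intervals, and the permutation and bounding analyses under Non-compliance are not said to use this SD. The article also does not say that the SD will be displayed as an interval or error bar. This part of the defence stands in full.

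**Conclusion.** The point holds as a mismatch between a stated formula and a stated quantity. As printed, the SD attached to each ATE is the spread of a unit-level difference with the covariance dropped. Taken literally it is about 4 to 6 times the standard error of the difference in averages. That range assumes equal SDs, one outcome per municipality and no allowance for blocking. Other assumptions move the multiple, from just under 4 to about 9.5 in the cases tried, but in none of them does the gap close. The multiple describes a literal implementation, not a result that the article reports.

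The harm is one of presentation and is limited to the descriptive step. Tests and confidence intervals are unaffected. The correction is still worth making, because the description as conservative gives a reader no reason to suspect a different quantity.

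**What to change.** For the ATE, replace the printed identity with a variance for the difference in averages, in one of two ways:

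- Var(Y_C)/n_C + Var(Y_T)/n_T, adapted to the state blocks and the known lottery probabilities. Each state has only one municipality in each audit arm, so a within-state variance for a single audit arm cannot be estimated; a block-adjusted version for such an arm would have to be built from the 17 state-level differences.
- The SD of the weighted difference over re-draws of the lottery, stating whether the re-draws assume no effect or a given additive effect. The planned randomization tests already rest on this assignment distribution.

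If unit-level spread was intended, keep it in a separate column, label it as such, say that it assumes zero covariance between the two potential outcomes, and do not call it the SD of the ATE. If Additional file 2 already states the correct variance, the article's sentence should be brought into line with it.

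The cost is one corrected sentence and formula. No new data are needed, and there is little computation beyond what is already planned.

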## Discussion

Randomized control trials are not immune from numerous threats to inference including attrition, non-compliance, and measurement error.

### Attrition

Attrition and missing outcomes can undo the benefits of randomization as observed outcomes may no longer be representative of the full experimental population nor comparable across observed experimental arms [53]. Due to small sample size we tried to prevent attrition by intensive follow up of non-respondents. We also collected logs of call efforts from the survey firm, under the assumption that those hardest to reach are similar to those never reached. We will also try to fill in missing response covariates (e.g. age, gender, and career history of of municipal official) using publicly available information. At the analytical stage we will do the following: Diagnosis: We will report the prevalence of attrition across experimental arms and check the covariate profiles of units missing outcomes versus those reporting outcomes. We will also check how observed outcomes vary with the recorded logs of call efforts.Hypothesis test: We will test the sharp null of no effect of treatment on attrition. Failure to reject the null that the treatment has no effect on the attrition strongly suggests that the observed units are at least comparable across treatment arms [53].Imputation: If the null is rejected then a complete data analysis is only appropriate if the outcome does not cause attrition and the only cause in common between the outcome and the attrition is the treatment [53]. This is a strong assumption. For robustness we will draw inferences using extreme bounds, and consider trimmed bounds, multiple imputations and inverse probability weights analyses as secondary analyses.

### Non-compliance

Non-compliance arises whenever experimental units receive a treatment different from the one assigned to them, and it can undermine the benefits of randomization [54]. For example, we know two municipalities could not be audited because of drug related violence. In addition, our partnership with the ASF allowed us to randomize the schedule of audits under the National Audits Program but EFSLs may choose to perform additional audits outside this program, though we do not expect two-sided non-compliance to be extensive. Because EFSLs report the complete list of municipalities they audit to the ASF so we will know the actual treatment status of all municipalities. To account for two-sided non-compliance we will proceed as follows: Using the treatment assignment variable test the sharp null of no effect (e.g. intention to treat analysis). If no null is rejected stop and declare the null of no treatment effect cannot be rejected. Otherwise proceed to estimation of effects.Estimate the ITT effect and, assuming monotonicity, the effect of treatment on the treated (ETT) using a permutation approach to instrumental variables [55]. (The latter is chosen for convenience as it is better adapted to dealing with the non-homogeneous randomization. If non-compliance is two-sided we will estimate the effect on compliers only).Report non-parametric natural bounds on the ATE [56].

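### ITT and ETT estimates and ATE bounds are produced only after a sharp null is rejected: this inflates estimates if the gate is per outcome, and leaves null results without intervals

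*Protocol article*

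**What the plan says.** The rule is in the Discussion, under Non-compliance. The sharp null is tested using assigned treatment. Then: "If no null is rejected stop and declare the null of no treatment effect cannot be rejected. Otherwise proceed to estimation of effects". The ITT estimate, the ETT estimate and the non-parametric bounds on the ATE are listed after that point.

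Statistical methods describes the general framework in the same spirit: "start by asking very little of the data, and then ask progressively more depending on the answers to previous queries". Its steps run from the sharp null test through plots and descriptive inference to modelling. The descriptive step gives group averages "along with the difference across averages and their standard deviations (so-called ATEs") and carries no explicit rejection condition. Intervals enter at the modelling step: "To generate estimates of causal effects and confidence intervals we need to assume non-interference and a model of causal effects". The stated default there is an additive effect with inversion of the sharp null test.

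Sample size says that no power analysis was done and adds, as a further check, ex post "power calculations for minimum detectable effect sizes for key outcomes".

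**The concern.** Making estimation depend on rejection is a significance filter. In a small trial, the estimates that pass are those that happened to land far from zero, so on average they overstate the effect. Their nominal 95% intervals can also cover the truth less than 95% of the time.

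Outcomes that do not pass are left with a statement that the null was not rejected. That statement cannot separate little or no effect from too little precision to tell. Both problems bear on this trial: it is exploratory, it has 17 municipalities in each audit arm, and its first two objectives are to identify the impacts of assignment, not merely to test for them.

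**Working it through.** **Inputs from the article.** 17 blocks of 5 municipalities at 1:1:3 give 17 federal audit, 17 state audit and 51 control: 17 + 17 + 51 = 85 = 17 × 5. The article gives no power figure to reproduce.

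**Assumptions.** The article states no alpha, SD or effect size. I take a two-sided 5% test (c = 1.96), outcome SD 1, no blocking, a separate gate for each outcome, and true effects δ of 0.2 to 0.8 SD.

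**Formulas.** With group sizes n₁ and n₂:

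- SE = √(1/n₁ + 1/n₂), and λ = δ/SE.
- Smallest significant estimate = c × SE. This is also the half-width of the 95% interval.
- Power = Φ(λ − c) + Φ(−λ − c).
- Exaggeration, the mean absolute significant estimate divided by δ = [λ{Φ(λ − c) − Φ(−λ − c)} + φ(c − λ) + φ(c + λ)] / (λ × power).
- Coverage given significance, for 0 < λ < 2c = [Φ(λ − c) − 0.025] / power.

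**Worked case: 34 v 51, δ = 0.3.** SE = √(1/34 + 1/51) = 0.221 and λ = 1.355. Power = 0.2726 + 0.0005 = 0.273. Exaggeration = [1.355 × 0.2721 + 0.3322 + 0.0016] / (1.355 × 0.273) = 1.90. Coverage = (0.2726 − 0.025)/0.273 = 0.91.

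**All contrasts, at δ = 0.2 / 0.3 / 0.5 / 0.8 SD:**

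| Contrast | SE | Significance threshold (SD) | Power (%) | Exaggeration (times truth) | Coverage at 0.3 SD |
|---|---|---|---|---|---|
| Both audit arms v control, 34 v 51 | 0.221 | 0.43 | 15 / 27 / 62 / 95 | 2.7 / 1.9 / 1.3 / 1.03 | 91% |
| One audit arm v control, 17 v 51 | 0.280 | 0.55 | 11 / 19 / 43 / 82 | 3.4 / 2.3 / 1.5 / 1.1 | 86% |
| Federal v state, 17 v 17 | 0.343 | 0.67 | 9 / 14 / 31 / 65 | 4.1 / 2.8 / 1.8 / 1.25 | 81% |

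The shortfall in coverage is mainly a small-effect result. At 0.8 SD, coverage given significance is 96 to 97% in all three contrasts.

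**Check by simulation.** A blocked permutation simulation (17 blocks, 1:1:3, 1,000 replicates, 399 permutations, equal assignment probabilities, no block effect) gave exaggeration of 2.7 / 1.9 / 1.27 / 1.04 for 34 v 51 and 3.5 / 2.4 / 1.5 / 1.1 for 17 v 51. The 17 v 17 contrast was not simulated. Without the filter, the mean 34 v 51 estimates were 0.204, 0.295, 0.491 and 0.809 for true effects of 0.2, 0.3, 0.5 and 0.8, so the inflation comes from the gate and not from the estimator.

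**If the gate is family-wide.** One rejection opens estimation for every outcome, so selection on each outcome's own result is weaker and the inflation is smaller than in the table. If nothing is rejected, the stop applies to all outcomes and none gets an ITT estimate or interval.

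**The case against.** Four points can fairly be made for the plan.

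- **Null outcomes are not left bare.** A reader might infer that no effect of any kind is shown without a rejection. The documents do not support that. The descriptive step in Statistical methods gives differences in means with standard deviations and states no rejection condition. This stands. Even so, that step belongs to a framework that will "ask progressively more depending on the answers to previous queries", and a difference with a standard deviation is not a confidence interval.
- **Ex post power is not offered in place of intervals.** A reader might infer a substitution from Sample size. The text calls the calculation an additional check, concerns minimum detectable effects rather than power at the observed effect, and does not tie it to null results. This stands in full, and the calculation is no part of the criticism.
- **The gate may be family-wide.** H1 is that treated administrators know their treatment status, and Blinding says municipal staff are clearly aware of being audited. If H1 counts toward the gate, it would open almost always and per-outcome inflation would largely vanish. The text does not settle this, so the inflation figures are conditional on the per-outcome reading.
- **A detailed analytical plan exists in Additional file 2, which is not shown.** It may tabulate intervals for all outcomes. The criticism here is of a rule the article itself states, not of something it leaves out.

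Blocking by state and several respondents per municipality are also ignored in the arithmetic. They could change the SE in either direction but do not remove the filter.

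**Conclusion.** The point holds in a limited form. The article explicitly makes the ITT, the ETT and the ATE bounds conditional on rejecting a sharp null, and it places confidence intervals at the last step of a conditional sequence.

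On the per-outcome reading, and under the assumed alpha and SD, inflation is material for true effects up to about 0.5 SD: 1.3 to 2.7 times the truth for 34 v 51, and 1.8 to 4.1 times for 17 v 17. At 0.8 SD it is negligible for 34 v 51 (1.03) and still 1.25 for 17 v 17. It would be wrong to say that reported estimates are always badly inflated or that their intervals always under-cover. On the family-wide reading the main loss is that a wholly null result carries no ITT estimate or interval.

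The two municipalities known not to have been audited would lower ITT power somewhat further.

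The stop rule is also unnecessary. The plan's default method, inverting the randomization test, gives an interval whether or not zero is rejected.

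**What to change.** Delete the stop rule as a condition for estimation. For every pre-specified outcome, report the ITT estimate with a 95% interval from the inverted randomization test, whatever the test result. Use the sequential procedure only to decide which hypotheses are claimed as rejected, and state whether that decision is made per outcome or across a family.

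Under the assumptions above, null outcomes would then carry intervals of about ±0.43 SD (34 v 51), ±0.55 SD (17 v 51) or ±0.67 SD (17 v 17), from which a reader can see which effects are excluded. These intervals rest on the same additive-effect and non-interference assumptions that the plan already makes. The ex post minimum detectable effect calculation can stay as the additional check it is described as.

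The cost is a change of wording and a longer results table. Type I error control is unchanged, because the tests and their order are not altered.
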